**Table 1 Tab1:**
[figure not shown]
Study assessments at specific time points.

**Fig. 1 Fig1:**
[figure not shown]
Flowchart of the Empower study

### Recruitment procedure

Participants will be recruited from the general community across Australia and the outpatient department at the Dubbo Hospital, Western New South Wales (NSW) Health District, NSW, Australia. All the trial procedures (e.g. eligibility screening, randomisation, baseline and follow-up questionnaires and study interventions) will be performed online.

Participants living in rural communities in Australia who are intending to seek care for their symptoms will be sought through the use of social media and printed advertisements. Advertisement flyers will be distributed through the University of Sydney platforms and relevant external organisations across Australia such as rural organisations, networks, councils, e-newsletter, etc. The online method of delivery will include email newsletters and social media platforms, including Facebook, and Instagram. Hard copies of advertisement flyers will be posted on public notice boards, placed in local businesses, and handed out at events (e.g. NSW Country Women’s Association) in rural Australia where potential participants can be identified. Study advertisements will direct individuals to a study website or to contact the research team to receive further information.

Individuals who are seeking care will also be identified from an outpatient physiotherapy department at a regional hospital in Dubbo, NSW. Individuals will be identified from the hospital’s waiting list or recent intake forms and contacted by hospital staff during a routine telephone call to schedule an appointment to be provided with information about the trial. If interested and verbal consent is provided, individual contact details will be entered into a secure REDCap (Research Electronic Data Capture) web survey by hospital staff. Individuals will then be directed to an online screening questionnaire, followed by a telephone screening to confirm eligibility, participant information sheet, consent form, and online baseline questionnaire.

### Randomisation and allocation

Randomisation will be blinded and performed using a computer-generated random allocation schedule operated centrally at the University of Sydney by a remote research assistant using the REDCap web application. Participants, hospital staff, and the eHealth physiotherapist will be notified, via automatic REDCap emails, about which group the participant has been randomly allocated. For participants recruited from the Dubbo hospital, a total timeframe of one week will be required to complete the recruitment and randomisation process.

### Blinding

Participants and physiotherapists will not be blinded to group allocation and will be aware of the alternative treatment components, but study hypotheses will not be disclosed to participants. The chief trial coordinator, the research assistant conducting baseline and follow-up collection, and statistician will be blinded to treatment allocation.

### EHealth intervention

Participants allocated to the eHealth intervention will schedule their first remote video consultation by email or telephone with the eHealth physiotherapist. The intervention includes a physical activity plan and a progressive resistance exercise program designed during remote video consultations with a physiotherapist using the Physitrack® Ltd., LDN, UK (physiotherapist end), and Physiapp® (participant end) web applications. Participants will be equipped with (i) a welcome booklet with an overview of the intervention components; (ii) instructions on how to use the Physiapp® web application (Web browser, Android or iOS app) at home; and (iii) an exercise kit consisting of a range of resistance bands. The intervention will be delivered over three months and guided by a maximum total of eight remotely-delivered video consultations in real-time with a physiotherapist. The initial consultation will last up to one hour, while subsequent consultations will be 30 min. The physiotherapist and patient will agree on the number of consultations according to the patient’s availability, with a minimum of 5 and a maximum of 8 video consultations being planned [33].

#### The home exercise program

During the physiotherapy video consultations, a home-exercise program will be designed according to patients’ preferences, individual goals, and the performance of remotely supervised exercises. The initial exercise prescription will have a dosage of two sets of 8–15 repetitions; 2 to 3-min rest in between sets; up to 4 total exercises to promote early adherence [34–36]; with a frequency of 3 times a week. Selected exercises will target the knee extensors and trunk musculature in both groups before further individualisation is made. After two weeks of familiarisation [37, 38] to promote early adherence, exercises will be performed to ≥5/10 (hard) on the modified Borg Rating of Perceived Exertion scale [39]. Resistance will be provided by using body weight or resistance bands to modify the difficulty of an exercise. The exercise dose used in this study is based on both the American College of Sports Medicine’s minimum recommendations for maintaining health [40] and previous studies using a similar intensity and frequency in non-specific chronic LBP and knee OA populations [17, 37, 39, 41, 42]. Modified exercises and dose will be provided for participants that have difficulties reaching this dosage initially or if, for example, muscular endurance is more appropriate. A 5–10 min warm-up and cool-down period will be included before and after each home exercise session focusing on joint range of motion and relaxation, respectively. Participants will be able to see the details of the exercise program, access video resources, record the details of each session and view their progress using the Physiapp® web application. Subsequent video consultations will allow to the physiotherapist to modify or make a progression of exercises if appropriate. Treatment fidelity will be assessed using a treatment note checklist within 24 h after each remote physiotherapy consultation. Table 2 shows a summary of how the exercise program is designed. Further details of the home-exercise program procedure can be found in online Additional file 2.

**Table 2 Tab2:** Home Exercise Program

**Exercise selection**	
Key prescription factors	• Patient goals • Patient preferences • Activity limitations
Body region	• At-least 1 exercise targeting the knee extensors • At-least 1 exercise targeting the trunk
Amount of exercises	• Minimum of 2 and Maximum of 4 exercises (initially)
Equipment used	• Patient surroundings, i.e. furniture, outdoor environment, access to any other exercise equipment such as a bike • Theraband® elastic band colour green
**Exercise dosage**	
Approximate intensity	• According to patient tolerance and symptomatology to exercise
Rated Perceived Exertion (RPE)	• At-least 5/10 RPE (hard)
Repetitions	• 8–15
Sets	• 2–3
Rest between sets	• 2–3 min
Frequency	• Three days per week (non-consecutive days)
Time period	• 3 months
Total consultation	• ≥5 consultations out of 8 offered
Familiarisation period	• Initial two weeks
**Modifications**	
Alternative	• Alternative dosage (if appropriate) - Isometric (30–60 s total hold time) - Endurance (15–25 repetitions)
Progression	• When the patient consistently over-performs above the prescribed dosage • Only one change at a time made when progressing
Simplification	• When the patient consistently underperforms below prescribed dosage (at least three consecutive sessions)
Examples of progression or simplification	• Adding or removing an exercise • Replacing an existing exercise • Changing the level of resistance band • Increasing or reducing isometric pauses • Modify surroundings or body position

#### The physical activity plan

The physical activity plan will be implemented according to the principles used in our previous study of physical activity for musculoskeletal pain [43]. The focus of the program will be on a gradual increase in physical activity where participants will be encouraged to devise fortnightly goals to suit and advance their physical activity levels. Each physiotherapist will be trained in the principles of health coaching to facilitate the process. The plan will be specifically tailored to each participant and will involve goal setting, monitoring, and progression of goals using the web application. Physical activity is prescribed according to the health coaching SMARTS goals, and it is tailored to each participant preference on the type of physical activity and functionality. It is also based on the World Health Organization guidelines, and they are not a goal itself but a desirable objective that will vary according to the participant’s previous physical activity levels and pain intensity. Further details of the physical activity plan can be found in online Additional file 2.

### Usual care group

The usual care provided in this trial is described as de facto usual care and includes the wide range of care practices provided in a community which are unrestricted by study protocols or rules [44]. This is in contrast to usual standardised care which may not reflect real-life care provided in the participating rural communities [44]. Due to the nature of de facto usual care and the dual recruitment strategy (general and hospital patient communities) used in this trial, therapy received by participants in this group will be self-reported using a weekly logbook throughout the study period. The specific treatments and care providers involved will vary depending on the participant’s location and source of recruitment. The common practice is likely to involve a visit to a primary care professional (e.g. GP, physiotherapist), prescription of pain medication, education, home exercises, and if within close vicinity to a health site, some additional supervised exercises tailored to the individual and may or may not involve additional manual therapy techniques.

All participants allocated into the usual care group will be contacted via telephone and email by a member from the research team who will liaise with the participant about what the planned care they were seeking for their LBP or knee OA. Participants recruited from the Dubbo Hospital outpatient physiotherapy department will have an appointment already scheduled and therefore, will only require a reminder and instructions to continue as usual. Participants recruited from the general community will be asked a series of questions about the health care site they were intending to access before entering the study. Assistance will be provided to those who are unaware of what options are available in their local community via a health service directory supported by the governments of Australia (https://www.healthdirect.gov.au/). A referral letter will then be provided to each participant, and the respective health care site mutually decided beforehand. Costs may be incurred to participants depending on their care pathway.

### Outcome measures

Outcome measures will be taken through an online link via REDCap at baseline, at 3 and 6 months follow-up post-randomisation.

#### Primary outcome

Physical function assessed using the Patient-Specific Functional Scale (PSFS) [45]; which ask participants to list three activities that they are unable to do are having difficulties because of their musculoskeletal pain. Each listed activity is then rated on an 11—point difficulty scale from 0 (‘unable to perform activity’) to 10 (‘100% able to perform the activity’). A total score ranging from 0 and 30 is calculated with higher scores indicating higher levels of physical function. This tool is valid and reliable for the evaluation of physical function in both people with chronic LBP [45] and those with knee OA [46].

#### Secondary outcomes

2.LBP or knee pain intensity over the past week assessed using an 11-point numeric rating scale (NRS) [47];3.Condition-specific activity limitation assessed using the Roland-Morris Disability Questionnaire (RDQ) [48] for LBP or the Western Ontario and McMaster Osteoarthritis Index (WOMAC) [49] for knee OA;4.Health-related quality of life measured using the Assessment of Quality of Life (AQoL)-8D instrument [50];5.Physical activity level assessed using the short-form of the International Physical Activity Questionnaire – Short Form (IPAQ-SF) [51];6.Pain self-efficacy measured using the Pain self-efficacy questionnaire [52].

#### Process evaluation measures

Measures of recruitment rate: during the recruitment stage of the trial, records will be kept regarding the number of participants screened for entry to the trial. If patients do not meet the study’s inclusion criteria, the reason they were ineligible for inclusion will be recorded. Similarly, if eligible, the reasons for declining participation in the trial will be noted.Measures of adherence: Both groups will receive a study paper-based logbook to record treatment details, medication use, adverse events, and health care travel details (See online Additional file 3). Participants will be provided with reply-paid envelopes for return of logbooks or will be provided with the opportunity to send them electronically. Participants in the eHealth intervention will be prescribed a total of 36 home exercise sessions over three months (three sessions per week). We will consider a self-reported number of completed exercise sessions converted to a percentage of total prescribed sessions. We will consider completion of 70% of prescribed home exercise sessions during the three months to be acceptable adherence [39].Measures of attendance: completion of the video consultation will be monitored and recorded by the eHealth physiotherapist. Participants in the control group will also report their attendance to a health care professional through the paper-based logbook.The measure of follow-up rate: the number of participants in each group who complete the baseline and follow-up assessments will be recorded. The reasons for the drop-out of participants will be recorded when possible throughout the different phases of this trial.The measure of opinion and perspectives: a phone interview will be used to investigate participants’ opinions and perspectives in both the eHealth and usual care group regarding the study. All participants who completed the study and those who dropped out will be invited to participate in the audio-recorded interview. They will be asked to rate their satisfaction on a scale from 0 (‘lowest satisfaction level’) to 10 (‘highest level of satisfaction’) regarding:
i)Overall experience with the study;ii)Accessibility of reaching the health professionaliii)Time to get an appointment with the health professionaliv)Cost of the intervention receivedv)The distance needed to travel for health carevi)Only participants in the eHealth group will be asked to rate their satisfaction with the Physiapp platform and exercise equipment provided.vii)Finally, all participants will be asked whether they would recommend the care to someone else.Difficulties and barriers to completing the trial: any issue experienced throughout the study will be recorded.

#### Other outcomes

7.The research team will closely monitor self-reported adverse events defined as increased musculoskeletal pain, trip/fall, serious events or other musculoskeletal symptoms assessed using a standardised weekly logbook. It will be recorded if the adverse event lasted more than 24 h and whether the participant required medical attention. Participants will be instructed to contact the study project manager if they believe any adverse event was caused by participating in the study.8.Medication and other health care use will be assessed using a weekly logbook.9.Distance travelled in kilometres to utilise health care (summed for all types of health care visits related to musculoskeletal pain) during the three month intervention period will be collected using the weekly logbook.

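### The adverse-event definition leaves out non-serious events that are neither musculoskeletal nor a trip or fall, so any harms summary by arm would be incomplete and could be distorted in an unknown direction

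*Protocol article*

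**What the plan says.** The definition is in the protocol article under Other outcomes: "self-reported adverse events defined as increased musculoskeletal pain, trip/fall, serious events or other musculoskeletal symptoms assessed using a standardised weekly logbook". Two further sentences follow. One adds detail to each event: "It will be recorded if the adverse event lasted more than 24 h and whether the participant required medical attention". The other gives a second reporting route: "Participants will be instructed to contact the study project manager if they believe any adverse event was caused by participating in the study".

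The same form goes to both arms. Process evaluation measures says: "Both groups will receive a study paper-based logbook to record treatment details, medication use, adverse events, and health care travel details". The form itself is an additional file that is not at hand. Medication is a separate item under Other outcomes: "Medication and other health care use will be assessed using a weekly logbook".

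On what the arms receive, Usual care group says common practice is likely to involve "prescription of pain medication, education, home exercises, and if within close vicinity to a health site, some additional supervised exercises tailored to the individual". The eHealth arm receives a physical activity plan and progressive resistance exercise. Table 2 sets the exertion at 5 out of 10 or more, labelled hard. Nothing in the article restricts medication in the eHealth arm.

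**The concern.** The list matches the usual non-serious harms of resistance exercise: more musculoskeletal pain, other musculoskeletal symptoms, and falls. It does not match the usual non-serious harms of pain medication, such as stomach upset or drowsiness, although the article names such medication as a likely part of usual care. It also omits symptoms of hard exercise that are not musculoskeletal, such as chest discomfort, breathlessness or light-headedness, unless they become serious.

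Two things are at stake. A harms summary by arm could give a wrong picture of the relative safety of the two approaches. Within the eHealth arm, early warning symptoms could go unrecorded as adverse events. Neither can be repaired in a later analysis plan, because events that were never collected cannot be analysed.

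**Working it through.** **Which events are counted.** The definition is set against the kinds of event that could occur.

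| Kind of event | Counted? |
|---|---|
| Serious, any body system | Yes |
| Trip or fall, any cause (including medication) | Yes |
| Non-serious, musculoskeletal | Yes |
| Non-serious, not musculoskeletal, not a trip or fall | No |

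**Whether another part of the article fills the last row.**

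- Duration over 24 hours and need for medical attention describe an event already counted. They do not widen the list.
- The route to the project manager applies to an adverse event, so it inherits the same definition.
- The medication item records use, not side effects.
- The process item on difficulties and barriers concerns completing the trial, not harms.
- Data integrity and monitoring gives an independent safety monitor a general remit, but no wider definition.

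None of these closes the gap.

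**Exposure without live supervision.** Process evaluation measures prescribes 36 home sessions, and EHealth intervention allows at most 8 video consultations. Even if every consultation coincided with a session, 36 - 8 = 28 sessions would be done without live supervision.

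**Size of a possible distortion.** The article gives no event rates, so there is no planned figure to reproduce and every rate below is an assumption. Let m be the proportion of an arm with a counted non-serious event (musculoskeletal or fall) and d the proportion with an uncounted one, independent within arm. Serious events are left aside because the definition already counts them. Then

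P(any) = 1 - (1 - m)(1 - d).

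The recorded difference, eHealth minus usual care, is m_E - m_C. The full difference is P_E(any) - P_C(any). For m = 30% and 20% with d = 10% and 20%:

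- eHealth: 1 - 0.70 × 0.90 = 37%
- usual care: 1 - 0.80 × 0.80 = 36%
- full difference +1 point, against +10 recorded.

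Other assumed rates, in percent (eHealth / usual care), with differences in percentage points:

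| m | d | P(any) | Recorded | All events | Recorded minus all |
|---|---|---|---|---|---|
| 30 / 20 | 5 / 10 | 33.5 / 28 | +10 | +5.5 | +4.5 |
| 30 / 20 | 10 / 20 | 37 / 36 | +10 | +1 | +9 |
| 30 / 20 | 10 / 30 | 37 / 44 | +10 | -7 | +17 |
| 30 / 20 | 5 / 30 | 33.5 / 44 | +10 | -10.5 | +20.5 |
| 30 / 20 | 10 / 10 | 37 / 28 | +10 | +9 | +1 |
| 30 / 20 | 15 / 15 | 40.5 / 32 | +10 | +8.5 | +1.5 |
| 30 / 20 | 20 / 10 | 44 / 28 | +10 | +16 | -6 |
| 25 / 25 | 10 / 20 | 32.5 / 40 | 0 | -7.5 | +7.5 |

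A positive last column works against eHealth and a negative one favours it.

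**What decides the sign.** Subtracting the two differences gives

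recorded minus all = d_C(1 - m_C) - d_E(1 - m_E).

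With m at 30% and 20% this is 0.80 d_C - 0.70 d_E. It turns in favour of eHealth once d_E exceeds 0.80 / 0.70 = 1.14 times d_C. The sign therefore depends mainly on which arm has more uncounted events, and the article does not give that.

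**The case against.** A reader might infer that the between-arm safety comparison is biased against eHealth. The documents do not support that as a fact, for three reasons.

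- The article describes no formal comparison of harms. Statistical analysis covers between-group models for continuous outcomes and does not mention adverse events.
- The arms differ only in degree. Usual care is also expected to include home exercise, possibly supervised exercise and manual therapy, which carry the musculoskeletal harms the list captures. Nothing stops eHealth participants from taking medication, and medication use is logged in both arms.
- The uncounted symptoms of hard exercise would make eHealth look safer, which is the opposite direction.

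All three points stand, and they remove any firm statement about direction.

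It can also be said that the logbook may have a free-text or other-event field, and that serious events, falls and health care use already pick up part of what is missing. Video consultations, each followed by a treatment note checklist, may bring further symptoms to light. This makes the practical gap smaller, but it does not change the stated definition. If the logbook does collect other events, the definition in the article disagrees with it and still needs correcting.

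Finally, adverse events are neither a primary nor a secondary outcome, and a targeted definition is a permissible design choice. That limits the weight of the point. It does not answer it, because the same adverse-event logbook goes to both groups and a summary by arm is its natural use. The gap in safety information within the eHealth arm exists without any comparison.

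**Conclusion.** The definition as stated omits non-serious events that are neither musculoskeletal nor a trip or fall, in both arms. This rests on the text alone. Any harms summary by arm would be incomplete.

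Distortion is possible. It works against eHealth if medication side effects are clearly more common in usual care, which is plausible from the description of that arm but not established. Under assumed counted rates of 30% and 20%, the gap between the recorded and the full difference runs from 1 point (uncounted events 10% in both arms) to 17 points against eHealth (10% and 30%), and reverses to 6 points in its favour (20% and 10%). More extreme assumptions give more extreme answers. These figures show how far the result depends on unknown rates, and they do not estimate the bias. They also assume independence of the two kinds of event within each arm.

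The point does not touch the primary outcome. It deserves correction because the loss cannot be recovered later and the remedy is cheap.

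**What to change.** Under Other outcomes, and in the logbook if it does not already do so, define an adverse event as any new or worsened symptom, injury or medical event in either arm, whatever the body system. Keep musculoskeletal pain, other musculoskeletal symptoms, trip or fall, and serious events as sub-categories. Add two: side effect of a medicine or other treatment, and other symptom (for example chest, breathing, dizziness, stomach). State that total and category-specific events will be reported by arm.

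The cost is a reworded sentence and a few extra categories in a weekly form that both arms already complete. The downside is that more minor, unrelated events will be recorded. Category-specific reporting keeps the events of most interest visible.
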